### Withdrawal

Withdrawal may be at an individual participant or care home level and from participation in delivery of the COG-D intervention (where relevant) and/or data collection. All participants will be informed they can withdraw from the study at any point without giving a reason and without it affecting their care/employment. Residents can choose to withdraw from completing the COG-D assessments but may agree to continuation of proxy data collection. Staff may decide to continue using the COG-D in their day-to-day practice if they decide to withdraw from intervention delivery and data collection. If a COG-D assessor does not wish to continue in this role, where feasible a new COG-D assessor will be identified and trained by the research team. Where a relative/friend wishes to withdraw in their role as personal consultee an alternative consultee (nominated consultee, generally a member of staff who knows the resident well) will be sought for ongoing advice.

Residents transferred out of the care home during the trial will not be considered as a withdrawal but termed as lost to follow-up. Researchers will document the date of transfer, and if transferred to a new care home will document the address to confirm if this care home is also taking part in the study. If transferred to another care home participating in the study, the resident’s participation will be reviewed, and relevant consent obtained (i.e., staff proxy informant).

### Data collection methods

As the COG-D intervention has not been tested in a cRCT in care homes to date, this study is designed to address specific areas of uncertainty about conducting a definitive trial of the intervention in this setting. Quantitative outcome data will be collected alongside an integrated mixed-methods process evaluation to explore the feasibility and acceptability of key study parameters and processes from the care home’s and resident’s perspectives.

#### Feasibility outcomes

Recruitment and retention of care homes, residents, and care-staff in both intervention and control conditions will be calculated to inform the number of care homes needed to achieve the target sample size for a future definitive trial. Acceptability, fidelity, and adherence to COG-D intervention protocol will be evaluated with completion rates for staff training and COG-D assessments, use and display of Daisies and revisions to care-plan based on COG-D assessments.

Feasibility of a Health Economic assessment will be explored in the ability to collect the data required (COG-D use, resource use, health and quality of life of residents) to undertake a cost-effectiveness analysis in the definitive trial and estimate potential costs and health benefits of the intervention.

Demographic data for residents (age, ethnicity, length of time in care home, gender, dementia diagnosis) will be collected from care plans. For staff, data will be obtained as part of the anonymous staff questionnaire (further training completed, duration of employment at care home) or in a short questionnaire preceding the staff training (role in care home, ethnicity (to explore diversity), age category, gender).

Candidate outcome measures for residents (by proxy) will be collected in interviews with researchers and staff outcomes are collected in the anonymous staff questionnaire (self-completed). Data completion rates of the candidate outcome measures (at each time point) will be calculated to determine which is the most appropriate primary outcome, agree other study measures and inform sample size calculation for the definitive trial.

#### COG-D assessment scores

(i) Scores from COG-D assessments and re-assessments to evaluate the sensitivity of COG-D to detect cognitive change in residents; (ii) enquiries or comments about cognitive change or requests for re-assessment by care-staff to compare with COG-D assessment results for evaluating the ability of staff to recognize changes in specific cognitive skills; (iii) Concordance rates between COG-D re-assessment scores of researchers and senior care-staff to evaluate ability/potential of staff to conduct assessments in the future CRT. The dementia severity questionnaire (Functional Assessment Staging of dementia (FAST) [20]) will be used to describe the study population and to explore associations between changes in the Cognitive Daisies and assessed dementia severity.

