##### COG-D assessments of residents

The COG-D assessments will be completed by a researcher and shadowed by senior staff who completed the Advanced COG-D Staff Training. The assessment tool COG-DAA constitutes 16 tasks, variants of which are routinely used for assessment of dementia and other neurological disorders. Assessments are conducted using the assessment booklet (A6 size), which allows assessment in a comfortable environment. A detailed COG-D assessment script is used with verbatim instructions for each test. The order of the tests allows for breaks without affecting performance. The test will be introduced as ‘puzzles’ or ‘activities’ to reduce any negative associations or performance anxiety. All materials are presented in a large font and line drawings are avoided (for instance, photographs of real objects are used for object naming and object recognition). A version for non-verbal responses is included to accommodate people with problems with speech production (COG-D SSP). Word lists for the different tests were carefully balanced in terms of age of acquisition, word-length, word-frequency, semantic category, and concreteness [15].

If the score for a test is below the cut-off score, the petal associated with the specific test is coloured. If the test cannot be completed, the petal will be grey. Daisies can be created in different ways to accommodate different uses. Assessors can choose to use a sticker system to create the Daisy together with the resident, or to create a digital version (using a web-based application) for inclusion in care plans (or both). For both methods, the Daisies can be produced without labels (for display) or with labels (e.g., for care plans). The digital version includes the pages of the Petal-By-Petal guide for the coloured petals. The study will explore how the different methods are used in the care homes.

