##### COG-D re-assessment of residents

Six months after the first COG-D assessment, residents will be re-assessed on COG-D by researchers and senior staff. Senior staff will be encouraged to lead the assessments and both assessors will score performance independently for concordance rates.

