### Intervention fidelity and adherence

Fidelity of the intervention will be optimized by using the same researchers for providing the Advanced Training in all intervention care homes and the same training materials for face-to-face and online training sessions for the Basic Training. COG-D assessors use a detailed COG-D assessment script with verbatim instructions for each test and detailed scoring instructions are provided. If COG-D re-assessments are led by senior staff, scoring is conducted independently by both assessors to ensure consistency. Fidelity and adherence will be monitored during the huddles and drop-in sessions where staff can ask questions and share good practice under supervision of the researchers. Fidelity and adherence will further be explored during the focus groups with staff during the process evaluation phase to inform the staff training and monitoring processes for the future trial.

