### Process evaluation

Following the MRC guidelines [21] on content of process evaluations, the aim is to explore context, implementation, and mechanisms of impact. Context (i.e., contextual factors and causal mechanisms that affect implementation, intervention mechanisms, outcomes) and mechanisms of impact (i.e., responses to and interactions with the intervention, mediators, unexpected pathways, and consequences) will largely be explored through semi-structured interviews/focus groups after final follow-up with (1) residents who completed the COG-D, (2) care home managers, (3) senior staff who completed the advanced training, (4) care-staff who completed the basic training, (5) relatives of residents who completed the COG-D. Questions will explore experiences of the COG-D implementation, perceptions of efficacy, barriers or facilitators to implementation and suggestions for revisions. Implementation (i.e., process of delivery and what is delivered) will be assessed through (1) audit of COG-D assessments—number of residents invited to complete, number completed initially and at re-assessment (dose, reach) and quality (fidelity), (2) care-plan review of consenting residents—transfer of assessment to care-plan (content, quality, extent), written evidence of implementation (fidelity, adaptations), (3) training records of numbers of staff trained at basic and advanced levels (implementation), (4) interviews/focus groups with care home managers, senior staff and care-staff.

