## Discussion

This feasibility study aims to explore the different pathways to impact of COG-D for residents and staff, and to determine to optimal protocol for investigating the effectiveness and cost-effectiveness of COG-D in a future large-scale cRCT in care homes. The inclusion of COG-D re-assessments at the end of the intervention period will provide valuable information about the sensitivity of the Daisies for monitoring change and fluctuations in cognitive functioning of residents with dementia in care homes [7–10]. It will be important to consider these fluctuations in the context of changes in health or medication and to explore the potential combined impact of both factors on independence in daily activities and the optimal way to evaluate this pathway in the future cRCT. Moreover, this information may be valuable for future studies investigating the potential benefits of COG-D in other social care settings and for supporting people with dementia living independently in the community and their family members.

Senior staff who complete the Advanced Training will be invited to lead the COG-D re-assessments with the residents. The proportion of senior staff who choose to accept this role (including facilitators and barriers thereof) will provide important information for further development of the optimal training protocol for the future large-scale RCT. Moreover, feedback from senior staff on the advanced training (in the post-training questionnaire) and their experiences in conducting COG-D assessments (post-trial interviews) will be instrumental in the development of train-the-trainer based training protocol to facilitate larger-scale dissemination of the COG-D package in care homes and other health and social care settings.

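### Same-session concordance at re-assessment measures scoring agreement only, so it cannot by itself show that staff can conduct COG-D assessments

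*Protocol article*

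**What the plan says.** Four places in the protocol article bear on this.

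- **COG-D assessments of residents** (first assessment): "The COG-D assessments will be completed by a researcher and shadowed by senior staff who completed the Advanced COG-D Staff Training". Staff produce no assessment of their own at this point.
- **COG-D re-assessment of residents** (six months later): "Senior staff will be encouraged to lead the assessments and both assessors will score performance independently for concordance rates".
- **Intervention fidelity and adherence**: "If COG-D re-assessments are led by senior staff, scoring is conducted independently by both assessors to ensure consistency". The same section describes the safeguard on delivery: "COG-D assessors use a detailed COG-D assessment script with verbatim instructions for each test and detailed scoring instructions are provided".
- **COG-D assessment scores**, item (iii), gives the use of the data: "Concordance rates between COG-D re-assessment scores of researchers and senior care-staff to evaluate ability/potential of staff to conduct assessments" in the future trial.

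Other evidence on staff is also planned. The Process evaluation section lists an audit of COG-D assessments that covers their quality, labelled as fidelity. The Discussion plans to look at the proportion of senior staff who take up the lead role, and at post-trial interviews about their experience of conducting assessments.

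**The concern.** Conducting a COG-D assessment has two parts: delivering the tests as scripted, and scoring the responses. The planned measure covers only the second, yet it is put forward as evidence on the whole task.

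Who led also matters. Staff are encouraged to lead but need not, and item (iii) neither restricts concordance to staff-led sessions nor splits it by leader. Sessions in which the researcher administered everything could then count towards a statement about staff conducting assessments.

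The study exists to inform the design of a definitive trial, and the Discussion looks ahead to train-the-trainer dissemination. A high concordance rate could be read as support for handing assessments to staff when nothing in it speaks to how staff delivered the tests. Departures from the script that are not recorded during the session cannot be recovered afterwards.

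**Working it through.** The article gives no concordance figure, target or statistic, so there is no number to reproduce. The check is a reading of the sections, followed by an illustration of the mechanism.

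**Step 1: how each pair of scores arises.** At the first assessment the researcher administers and staff shadow. At re-assessment both people are present and score the same performance. No separate staff-conducted and researcher-conducted assessment of the same resident is described. Re-assessment is thus the only described occasion on which staff may administer the tests to trial residents, and every pair of scores comes from one shared administration.

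**Step 2: which sessions enter the rate.** The re-assessment section reads as double scoring of every session. The fidelity section mentions double scoring for staff-led sessions and gives its purpose as consistency. Item (iii) sets no restriction. Whether researcher-led sessions count is left open.

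**Step 3: what shared-session agreement can detect.** Take one petal that is coloured or white. None of the following values is in the documents.

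- s = probability that a scorer errs, independently for the two scorers: 2% or 5%.
- a = probability that staff administration alters the resident's result: 0, 5, 10 or 20%.
- The resident does not change between sessions, and scoring error does not depend on administration error.

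In a shared session the two scores agree when both scorers are right or both are wrong:

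shared = (1 − s)² + s²

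The term a does not appear. For a staff-led session compared with a separate, correctly administered one:

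separate = ½ × [1 + (1 − 2s)² × (1 − 2a)]

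The gap between the two is a × (1 − 2s)².

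| s | a | shared (%) | separate (%) | gap (points) |
|---|---|---|---|---|
| 2% | 0 | 96.08 | 96.08 | 0 |
| 2% | 5% | 96.08 | 91.47 | 4.61 |
| 2% | 10% | 96.08 | 86.86 | 9.22 |
| 2% | 20% | 96.08 | 77.65 | 18.43 |
| 5% | 0 | 90.50 | 90.50 | 0 |
| 5% | 5% | 90.50 | 86.45 | 4.05 |
| 5% | 10% | 90.50 | 82.40 | 8.10 |
| 5% | 20% | 90.50 | 74.30 | 16.20 |

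Worked case, s = 2% and a = 10%: shared = 0.98² + 0.02² = 0.9608; separate = ½ × (1 + 0.9216 × 0.80) = 0.8686; gap = 0.10 × 0.9216 = 0.0922. A simulation under the same assumptions gives the same agreement figures to within rounding, whether 30% or 50% of petals are coloured.

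Shared-session agreement does not change as administration gets worse. Under these assumptions it is an upper bound on agreement between separately conducted assessments, and the bound is met when a = 0.

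**The case against.** The strongest reply is that concordance is one strand among several and that delivery is well protected. Administration is scripted, scoring instructions are detailed, senior staff have advanced training, and a researcher attends each re-assessment. The wording is ability or potential, and correct scoring is a necessary part of both, so even a researcher-led session has some bearing on potential. The quality audit, uptake of the lead role and the interviews add further evidence. Concordance is not among the progression criteria in Table 2, and no decision rule is tied to it.

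Most of this stands, and it limits the weight of the point. It does not remove it. A script limits administration error but does not measure it. Uptake shows willingness, and interviews report experience. The huddles and drop-in sessions are for questions and shared practice. The audit could cover administration, and its method may well be in the full protocol, but the article describes no observation of staff delivering the tests. None of these makes shared-session concordance informative about delivery.

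A reader might go further in three ways that the documents do not support.

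- **That concordance will overstate staff ability.** This needs an administration error rate above zero, and the documents give none.
- **That the re-assessment and fidelity sections contradict each other.** The fidelity section does not say that double scoring happens only when staff lead. Its statement fits inside the broader one, so this is an ambiguity.
- **That a raw concordance rate would be inflated by chance agreement.** The share of coloured petals is not given, the text speaks of scores and does not say that agreement will be on petals, and the choice of agreement statistic is commonly left to the analysis plan.

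**Conclusion.** The point holds in a limited form. Concordance from two people scoring one session supports a statement about scoring agreement. It cannot detect administration error, and item (iii) does not separate sessions by who led. Used as evidence on conducting assessments, it may overstate ability by an amount that cannot be estimated from the documents. The illustrated gaps of 0 to about 18 percentage points rest wholly on assumed error rates and show the mechanism, not an expected size. The structural part, that shared-session agreement does not respond to administration error, needs only that scoring error is unrelated to how the test was delivered.

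This is a cheap improvement worth making before re-assessments take place. It does not threaten the feasibility conclusions tied to Table 2.

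**What to change.** 1. Align the sections on re-assessment, on fidelity and adherence, and on COG-D assessment scores so that they state which re-assessments are double-scored.
2. Label same-session concordance as scoring agreement, and report it separately for staff-led and researcher-led sessions.
3. Base any statement about staff conducting assessments on staff-led sessions, and give the number and share of sessions that staff led. The uptake figure planned in the Discussion is per staff member, so it does not supply this.
4. In staff-led sessions, have the researcher who is already present mark, test by test, any departure from the verbatim script. Report the share of tests delivered as scripted and feed it into the fidelity audit under Process evaluation.

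The cost is a lead-assessor field, a tick column on the existing script and a small amount of extra tabulation. The drawback is that the figure on staff ability will rest on fewer sessions.

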#### Care-plan audit

Conducted pre-post intervention to evaluate if COG-D influences entries in residents’ care-plans. COG-D sheets for care plans accommodate adding resident-specific recommendations for different situations (personal care, mealtimes, scheduled activities). Completion rate and content of these added recommendations will be analyzed. Other sections will be analysed for use of COG-D related terminology (e.g., domain label use to refer to cognitive problems) in relation to suggested changes in care. This analysis will be conducted for all residents for whom consent will have been obtained (whether they complete the COG-D assessment or not) to evaluate transfer of knowledge.

### Process evaluation

Following the MRC guidelines [21] on content of process evaluations, the aim is to explore context, implementation, and mechanisms of impact. Context (i.e., contextual factors and causal mechanisms that affect implementation, intervention mechanisms, outcomes) and mechanisms of impact (i.e., responses to and interactions with the intervention, mediators, unexpected pathways, and consequences) will largely be explored through semi-structured interviews/focus groups after final follow-up with (1) residents who completed the COG-D, (2) care home managers, (3) senior staff who completed the advanced training, (4) care-staff who completed the basic training, (5) relatives of residents who completed the COG-D. Questions will explore experiences of the COG-D implementation, perceptions of efficacy, barriers or facilitators to implementation and suggestions for revisions. Implementation (i.e., process of delivery and what is delivered) will be assessed through (1) audit of COG-D assessments—number of residents invited to complete, number completed initially and at re-assessment (dose, reach) and quality (fidelity), (2) care-plan review of consenting residents—transfer of assessment to care-plan (content, quality, extent), written evidence of implementation (fidelity, adaptations), (3) training records of numbers of staff trained at basic and advanced levels (implementation), (4) interviews/focus groups with care home managers, senior staff and care-staff.

### Data management

HHTU will provide the data systems including a study database built with REDcap cloud EDC, and box file storage system which are both within scope of the HHTU NHS Data Security and Protection Toolkit (Organization Code EE133824-HHTU). Questionnaires can be completed electronically by the researcher or staff directly into REDcap cloud. If paper versions of the questionnaires are used, the responses will be entered into the COG-D data base by a member of the research team. Completed paper versions of the staff questionnaire (PIS and consent form integral) can be sent directly to UoL in self-addressed envelopes or dropped off at the care home in a secure box. Paper copies of data collection forms will be stored in a lockable filing cabinet at the University of Lincoln in a restricted access room and will be identified by a unique study number (study ID) that is assigned when participants consent at baseline. Signed consent forms (including nominated consent) for residents will be stored separately from paper data collection forms as they will contain identifiable information.

Healthcare records of residents will only be accessed by the researcher with consent from the participant (or their consultee). A small amount of identifiable data (e.g., name) will be held to link the resident with their health and social care records (participants with dementia). No directly identifiable personal data of staff will be recorded.

#### Audio recordings

For participants who consent to take part in interviews and focus groups, personal contact details will be stored on the HHTU instance of Box. Interviews will be recorded using an encrypted Dictaphone with the data file uploaded to Box as soon as possible. The file will be deleted from the Dictaphone once the upload is completed. Transcripts will be identified using study ID with other identifying information removed, and only anonymized quotes from interviews and fieldnotes will be used to illustrate themes of analysis.

### Confidentiality

Access to personal data will be limited to authorized members of the research team. All research staff working on COG-D will be required to work to the HHTU Confidentiality Code of Conduct and Confidentiality Audit Procedure. Data will be held in accordance with the General Data Protection Regulation (GDPR 2018). The study will be conducted in compliance with Good Clinical Practice (GCP) and the current approved protocol.

The HHTU EDC system is encrypted in transit and rest, sites can only view and enter data related to their own patients. It offers a robust audit log of data/time/user access and IP is maintained that shows all changes to data records within the system—all access in the system is tracked. Any datasets exported for analysis will be pseudo-anonymized with data identified by study ID.

